**Demographics**					
	Demographics, socioeconomic status, ethnicity, household composition, and pets	✓	—^a^	—	—
**Physical health**					
	Medical health	✓	✓	✓	✓
	Medication and supplement use	✓	✓	✓	✓
	Oral health	✓	—	✓	—
	ROME III Diagnostic Questionnaire for Adult Functional Gastrointestinal Disorders	✓	—	✓	—
	Childbirth details	—	—	✓	
	Anthropometrics: body mass index, weight, height	✓	—	✓	✓
	Head circumference	—	—	✓	✓
**Maternal psychological well-being and relationships**					
	The Edinburgh Postnatal Depression Scale [42]	✓	—	✓	—
	Depression Anxiety and Stress Scale-21 [43]	✓	✓	✓	—
	Perceived stress scale [44]	✓	—	✓	—
	Big-5 personality scale [45]	✓	—	—	—
	Multidimensional scale of perceived social support [46]	✓	—	✓	—
	Nature relatedness scale [47]	✓	—	✓	—
**Diet**					
	Dietary Questionnaire for Epidemiological Studies (Version 2) [24]	✓	—	✓	—
	Simplified Dietary Questionnaire [26] (modified)	✓	✓	✓	—
	Probiotic Food and Drink Questionnaire	✓	✓^b^	✓	
	Infant diet	—	—	—	✓
**Lifestyle**					
	International Physical Activity Questionnaire [48]	✓	—	✓	—
	Smoking	✓	—	✓	—
**Process evaluation**					
	Workshop evaluation	—	✓^b^	—	—
	Study evaluation	—	—	✓	—
	General self-efficacy scale [49]	✓	—	✓	—
	Motivation and readiness to change [50]	✓	✓	✓	—
	Intervention personal goals	—	✓^b^	—	—

^a^Not collected.

^b^Intervention group only.

**Table 2 table2:** Biological sample collection schedule.

Measurement		Baseline (gestation week 26; mother)	Follow-up (4 weeks postpartum)	
			Mother	Infant
**Microbiota and metabolites**				
	Stool sample	✓	✓	✓
**Stress and inflammatory markers**				
	Saliva	✓	✓	—
	Guthrie spot	—^a^	—	✓
**Epigenetic regulation**				
	Buccal cells	✓	✓	✓

^a^Not collected.

### Data Management and Access

Questionnaires were administered electronically to participants through REDCap [28], which is hosted on secure servers at MCRI. Information is kept confidential through a secure password-protected system and restrictive user-access permissions. Study team access to participant information was strictly limited to the purposes of running the study, such as organizing study visits, support calls, and recording biological sample collection. For analysis, the investigators have access to the final deidentified trial dataset.

### Monitoring

Being a community-based health intervention, minimal harms are foreseen. No independent bodies were developed for data monitoring or auditing trial conduct. Any adverse events would be reported to the Human Research Ethics Committees (HRECs) in accordance with the safety reporting policy of the HREC. [name] oversaw the implementation of the study, and the HRECs of The Royal Children’s Hospital and Deakin University review its progress.

### Availability of Data and Materials

Data sharing is not applicable, and no data have been reported.

### Statistical Methods

The study results will be reported in accordance with the Consolidated Standards of Reporting Trials (CONSORT) guidelines [51]. Analyses will be performed according to a modified intention-to-treat principle, in which participants with at least 1 valid postbaseline follow-up are included.

#### Primary Outcome

The infant Shannon Diversity Index (collected 4 weeks after birth) will be calculated using the phyloseq R package [52]. Normal distribution will be assessed by visually inspecting quantile-quantile plots. If data are normally distributed, then an independent student *t* test will be conducted, otherwise a Wilcoxon-Mann-Whitney U test will be conducted to determine between-group differences, where statistical significance is considered at the P<.05 level [53].

#### Additional Multivariable Analysis

Additional multivariate analysis will be performed to examine potential effect modifiers (sample storage duration, birth mode, antibiotic exposure, gestational age, and mode of feeding) using Kraemer et al’s [54] approach as a guideline.

#### Secondary Outcomes

#### Gut Microbiota

Infant stool alpha diversity will be further analyzed using 4 other measures (Inverse Simpson, Chao1, phylogenic diversity, and observed species) using the same methods described for the primary outcome. All 5 alpha diversity measures will be analyzed for mothers adjusting for baseline measures. Further analyses will examine potential effect modification for storage duration, baseline, antibiotic, and medication use in accordance with Kraemer et al [54]. Between-group differences in the relative abundance of genus *Prevotella* will be analyzed using the same methods described for the primary outcome for infants and a baseline-adjusted method for the mothers.

A total of 2 beta diversity metrics will be calculated (Generalized UniFrac distances [55] and Bray-Curtis dissimilarity.) Group-based separation will be visually inspected using principal coordinates analysis and constrained ordination plots of these beta diversity metrics. Further plots will be created to inspect separation based on potential effect modifiers: mode of birth, antibiotics, sample collection week, and mode of feeding. Permutational multivariate analysis of variance (PERMANOVA) [56] with 999 permutations will be used on the beta diversity metrics to determine the statistical significance of group-based separation. In a secondary analysis, these PERMANOVA models will test for the aforementioned potential effect modifiers. Differential abundance testing with a false discovery rate correction will be performed to explore OTUs that are different between groups. The appropriate transformation and test will be determined in accordance with Weiss et al once library size is known [57]. For significant outcomes, the role of dietary change or probiotic or prebiotic supplementation in potentially mediating microbial outcomes will be examined.

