#### Sample Size and Power

The study was powered to detect a between-group difference in alpha diversity (Shannon index) in infants. At design time in 2015, very few studies reported infant alpha diversity measured at 4 weeks, and no studies that we are aware of have ever reported differences in infant alpha diversity as a function of a maternal dietary intervention; thus, it was difficult to estimate an expected change. Instead, a clinically relevant difference in Shannon index was determined based upon the small number of case-control studies reporting differences between the Shannon index of healthy 4-week old infants to those with health problems (such as allergy) [2,4,27]. Across these studies, the mean between-group difference in Shannon index ranged between 0.2 and 0.3. Standard deviations were derived for each group ranging between 0.2 and 0.5, with 0.4 being most common. On the basis of these data, the sample size was calculated using the power.*t* test function of the R *stats* package (R Core Team, version 3.2.0). A sample of 80 mothers would provide 80% power to detect a difference in Shannon index of at least 0.25, assuming a standard deviation of 0.4 and a 2-sided type I error of 0.05. Therefore, 90 pregnant women would be recruited to participate, this permitted a loss to follow-up of 10 participants (12.5%).

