### Randomization

The randomization process used a concealed 1:1 group allocation ratio with randomly permuted block sizes to ensure allocation was unpredictable. External personnel prepared the randomization schedule and applied it to the Research Electronic Data Capture (REDCap) randomization module [28]. The study administrator used REDCap to randomly allocate each participant. After allocation, blinding was no longer possible because the team had to book study visits or a workshop.

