Regardless of a participant’s baseline diet quality, we expect that the intervention will be effective in increasing average intakes of fiber, and prebiotic, and probiotic foods. These foods were specifically targeted in the intervention, while the control group was unaware of the interest in these prebiotic and probiotic foods. We anticipate that the diversity of the prenatal gut microbiota is stable and will respond to this dietary change. DiGiulio et al demonstrate that stool alpha diversity is stable from week-to-week during pregnancy and the postpartum period [59]. Elsewhere, Koren et al report that there is significant instability during pregnancy [60]. However, samples were only collected at 3 time points (not weekly), and critically, a subset of participants may have been involved in a dietary intervention consuming probiotics [61]. In nonpregnant adults, gut microbiota respond to short-term dietary intake within 24 hours [62,63]. Hence, dietary change needed to be sustained through to follow-up when the final stool sample was collected. We addressed this in our intervention design through the use of BCTs [21,39], and during the last support call (before birth), we discussed how each participant plans to sustain their dietary goals after birth (Multimedia Appendix 3).

The study is powered to test for an overall effect of the intervention. The overall intervention effect will be unbiased on the basis that the study has an RCT design, where we expect that potential effect modifiers or confounders (both measured and more importantly unmeasured) will be balanced out between groups. The study will not be underpowered unless there is strong heterogeneity because of a potential effect modifier. Based upon the population rates, we expect the majority of births to be vaginal, and majority of infants will be breast fed (67% vaginal birth, 33% cesarean [64], with 74.6% breastfeeding at 1 month [65]). The study may not have power to detect the role of effect modifiers, but this was not the main study aim. Our sample size calculation was based upon an estimated standard deviation of 0.4, we recently reassessed the accuracy of this estimate using recently available 16S data for 144 4-week old infants from the INFANTMET cohort [66]. We analyzed these data and arrived at a standard deviation of 0.317; this is lower than our original estimate, indicating that our sample size calculation may be conservative.

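### Standard PERMANOVA is planned for birth mode and feeding mode, whose expected groups are unequal, so a difference in dispersion can pass for, or hide, a shift in composition

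*Protocol article*

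**What the plan says.** The Gut Microbiota part of Secondary Outcomes names Generalized UniFrac and Bray-Curtis as the beta diversity metrics and fixes PERMANOVA with 999 permutations as the test of separation between arms. Plots are planned by "potential effect modifiers: mode of birth, antibiotics, sample collection week, and mode of feeding". In a secondary analysis, "these PERMANOVA models will test for the aforementioned potential effect modifiers". The article does not say whether this means main effects of the modifiers or arm-by-modifier interactions.

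The Discussion gives the expected distribution of two of these factors, taken from population rates: "67% vaginal birth, 33% cesarean [64], with 74.6% breastfeeding at 1 month [65". No split is given for antibiotics or sample collection week. The Randomization section says "The randomization process used a concealed 1:1 group allocation ratio with randomly permuted block sizes", so equal group sizes are designed in for the arms only.

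**The concern.** PERMANOVA is meant to detect a difference in location between groups in the space of the distance matrix. Its permutation null is that observations are exchangeable between groups, and this fails if the groups differ in spread even when their centroids coincide. With equal group sizes the consequence is small. With unequal sizes the test rejects too often if the smaller group is the more dispersed, and too rarely if the larger group is.

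The protocol therefore commits a named test to two factors that it expects to be unequal in size. A significant result for birth mode or feeding mode could reflect only that one group is more heterogeneous, and a null result could hide a real shift. At stake is how the modifier results for the infant microbiota are read, not the trial's main conclusion.

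**Working it through.** **Inputs from the article.** Analysable sample 80 (Sample Size and Power); splits 67/33 and 74.6/25.4 (Discussion); 1:1 allocation (Randomization). **Assumed, because the article gives no figure:** the dispersion ratio r = SD of smaller group / SD of larger group; two-level coding of feeding; Euclidean data.

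**1. The plan's own figure.** The article says "A sample of 80 mothers would provide 80% power to detect a difference in Shannon index of at least 0.25", with SD 0.4 and two-sided alpha 0.05. With 40 per arm, 0.25 / (0.4 × √(2/40)) = 0.25 / 0.0894 = 2.795, and 2.795 − 1.960 = 0.835, so power is about 79.8% (78.8% with the t distribution). The figure of 80 is sound to within rounding and is used below. The article states no error rate for the PERMANOVA tests.

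**2. Group sizes.** 0.67 × 80 = 53.6, giving 54:26. 0.746 × 80 = 59.7, giving 60:20.

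**3. Why imbalance matters.** Let the larger group (n₁) have total variance 1, the smaller group (n₂) have total variance r², and the centroids be equal. The expected between-group sum of squares (1 df) is n₂/N + r²·n₁/N. The expected within-group mean square is [(n₁ − 1) + r²(n₂ − 1)] / (N − 2). Their ratio should be about 1 under the null.

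- 40:40, r = 1.5: (0.5 + 2.25 × 0.5) / [(39 + 2.25 × 39)/78] = 1.625 / 1.625 = 1.00
- 54:26, r = 1.5: (0.325 + 2.25 × 0.675) / [(53 + 2.25 × 25)/78] = 1.844 / 1.401 = 1.32
- 60:20, r = 1.5: (0.25 + 2.25 × 0.75) / [(59 + 2.25 × 19)/78] = 1.938 / 1.304 = 1.49
- 54:26, r = 0.667 (r² = 0.444): 0.625 / 0.822 = 0.76
- 60:20, r = 0.667: 0.583 / 0.865 = 0.67

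The permutation distribution is centred near 1 in every case. The observed statistic is therefore centred too high or too low as soon as sizes and spreads both differ, and is centred correctly if either is equal.

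**4. Simulated type I error.** Equal centroids, N = 80, standard pseudo-F, raw permutation, nominal 5%. Ranges cover several Euclidean structures (10 or 20 equal axes; 50 axes with variances falling as 1/k). The main runs used 500 data sets per cell; Monte Carlo error is about 1 point near 5% and 2 points near 30-50%.

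| Assumed r | 54:26 | 60:20 |
|---|---|---|
| 0.67 | 0-2% | 0-2% |
| 1 | 4-5% | 5-7% |
| 1.25 | 10-16% | 12-21% |
| 1.5 | 15-25% | 23-36% |
| 2 | 27-29% | 45-51% |

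The rows for r = 1 and r = 2 were run on two structures only (10 equal axes; 50 axes with 1/k variances). A balanced 40:40 split stayed within about 3-8% at every ratio tried. The 1:1 arm term, tested in the same models, stayed at 3-7%.

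**5. Sensitivity.**
- *Dimension.* At 53:27 and r = 1.5, the error was about 12% with 3 equal axes, 15% with 10, 22% with 20 and 37% with 50. At r = 1.1 with 20 axes it was about 7%.
- *Interaction.* At r = 1.5 the arm-by-modifier term rejected in 13-24% (54:26) and 26-38% (60:20) of Euclidean runs. With Bray-Curtis distances on simulated compositions it rejected in 11-12% at the unbalanced splits and 5% when balanced. The Bray-Curtis main effect was not a clean null, because changing the spread also moved the centroid, so it is not used.

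**6. Does the alternative help?** A Welch-type distance statistic with the same permutations gave 3-8% across the unbalanced Euclidean cells.

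**The case against.** The strongest reply is that this is an omission. A dispersion check is a routine companion to PERMANOVA, a journal article may leave it to the full protocol, and nothing in the article rules it out. That is fair: the missing check is not itself an error. What remains is that the article does state the test and the expected imbalance, and that for two-group main effects a concrete alternative behaves better. The planned ordination plots may show unequal spread, but they do not correct the P value.

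Second, the percentages are not properties of this trial. The dispersion ratio is assumed, the distances were mostly Euclidean, the splits are population rates, and feeding may have more than two levels. This stands, and it is why ranges are given. If the modifiers are tested only as interactions, the one Bray-Curtis check suggests a smaller distortion.

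Third, the stakes are limited. The Discussion says that the modifiers were not the main aim and that power for them may be lacking. This also stands, although low power is a different matter from false positives.

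A reader might infer that the arm comparison is compromised as well, or that the authors rely on 1:1 allocation to justify PERMANOVA for the modifiers. The documents support neither. The arm groups are equal by design, and the article mentions the ratio only as a feature of randomization.

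**Conclusion.** The concern holds in conditional form. Standard PERMANOVA is fixed for birth mode and feeding mode, which the article expects to be unequal in size, and at those sizes its error rate depends on relative dispersion. If the smaller group's SD is 1.25 to 1.5 times that of the larger, a nominal 5% test rejects about 10-25% of the time at 67/33 and 12-36% at 75/25. If the ratio is 0.67, it rejects about 0-2% of the time and loses power. If dispersions are equal, there is no problem.

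It would go too far to say that the modifier tests will give false positives: the article does not show that dispersions differ, or in which direction. The conclusion rests on 80 analysable infants, two-level feeding and the population splits holding in this sample. It concerns a secondary analysis of a secondary outcome. The primary Shannon comparison and the arm PERMANOVA are unaffected. This is a worthwhile refinement, not a flaw that threatens the trial.

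**What to change.** - For each categorical modifier, report a permutation test of homogeneity of multivariate dispersion (999 permutations) on the same Generalized UniFrac and Bray-Curtis matrices.
- For two-group main-effect tests of unbalanced modifiers, such as birth mode and two-level feeding, use a Welch-type distance statistic with the same permutations in place of the standard pseudo-F.
- The one-way Welch statistic does not apply to arm-by-modifier interactions or to a continuous factor, as collection week may be. There, report the dispersion result for the categorical modifiers, and do not read a significant PERMANOVA as a compositional shift when dispersions differ.
- State whether main effects, interactions or both are tested, since this decides which of these rules applies.

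The cost is a few lines of code on distance matrices that will exist anyway, slightly more output, and a small loss of power if dispersions are in fact equal. The article says that the results are still to be written, so the choice can be recorded before these tests are reported.

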#### Intervention Efficacy and Dietary Intake

Linear mixed model analyses using the generalized estimating equation (GEE) technique will be used to evaluate between-group baseline-adjusted mean differences, accounting for within participants autocorrelations across multiple time-points, for the 14 DGI-13 long-term diet measures [23], 6 macronutrient measures [24], and the 13 SDQ short-term diet measures [26]. All tests will be 2-sided, and statistical significance is considered at a P value <.05. No correction for multiple comparison will be implemented for these outcome analyses as these comparisons are *a priori* research questions with specified alternative hypotheses. Time trends in short-term diet quality and intakes of prebiotic and probiotic foods are evaluated from baseline to before birth, and baseline to after birth. For significant outcomes, the role of motivation or mental well-being in potentially mediating any impact of the intervention on dietary intake will be examined.

Analysis plans for all nonmicrobial secondary outcome measures including SCFAs, inflammation, epigenetic regulation, behavior change, well-being, feasibility, and acceptance are detailed in Multimedia Appendix 5.

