#### Diet

Women in the intervention group will (1) improve their diet in accordance with the Australian dietary guidelines; (2) consume a wider variety of foods; and increase intakes of (3) fiber, (4) prebiotic foods, and (5) probiotic foods compared with the control group, and these changes will be sustained throughout pregnancy. The intervention group will reduce intakes of (6) refined processed foods, (7) saturated fat, and (8) total energy compared with the control group. 

Further secondary hypotheses for other biological outcomes (ie, short chain fatty acid [SCFA] concentration, inflammation, stress, and epigenetic regulation) and study feasibility are listed in Multimedia Appendix 1.

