#### Dietary Intake

Long-term (3-month) maternal dietary quality and variety are evaluated by applying the Dietary Guideline Index 2013 (DGI-13 scores) [23] to the validated Dietary Questionnaire for Epidemiological Studies v2 (DQES) [24], measured at baseline and 4 weeks after birth. DGI-13 scores include a total diet quality score and 13 subscores to evaluate each dietary guideline [25]. Daily macronutrients from the DQES are energy (kilojoules; kJ), protein (kJ), carbohydrate (kJ), fat (kJ), saturated fat (kJ) and fiber (grams). Time-related trends in short-term (2-week) diet quality and intakes of prebiotic and probiotic foods are evaluated using a version of the Simplified Dietary Questionnaire (SDQ) [26] modified to include prebiotic and probiotic foods. SDQ scores include a total diet quality score and comprises a dietary variety score and 9 subscores evaluating each guideline [25], along with 2 additional scores for prebiotic and probiotic food intake.

Further secondary outcome measures for other biological outcomes and study feasibility are listed in Multimedia Appendix 2.

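### Thirty-three diet measures are tested at P<.05 without correction because all are said to have specified alternatives; three have none and 22 subscores share at most an umbrella hypothesis

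*Protocol article*

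**What the plan says.** The section Intervention Efficacy and Dietary Intake plans baseline-adjusted between-group comparisons "for the 14 DGI-13 long-term diet measures [23], 6 macronutrient measures [24], and the 13 SDQ short-term diet measures [26"]. Tests are two-sided with significance at P<.05. It then states "No correction for multiple comparison will be implemented for these outcome analyses", on the ground that the comparisons are a priori questions for which alternatives have been specified. Diet outcomes that reach significance go on to an analysis of motivation or mental well-being as mediators.

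The measures are defined under Secondary Outcome Measures, Dietary Intake:
- DGI-13: "DGI-13 scores include a total diet quality score and 13 subscores to evaluate each dietary guideline".
- Macronutrients: "energy (kilojoules; kJ), protein (kJ), carbohydrate (kJ), fat (kJ), saturated fat (kJ) and fiber (grams").
- SDQ: a total score that "comprises a dietary variety score and 9 subscores evaluating each guideline [25], along with 2 additional scores for prebiotic and probiotic food intake".

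The alternatives are under Secondary Hypotheses, Diet, which numbers eight. The first five are better accordance with the national guidelines, wider variety, and more fiber, prebiotic foods and probiotic foods. The last three read: "The intervention group will reduce intakes of (6) refined processed foods, (7) saturated fat, and (8) total energy compared with the control group". The same section sends to Multimedia Appendix 1 only the hypotheses on other biological outcomes and on feasibility, so nothing in the article points to further diet hypotheses there.

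**The concern.** The waiver depends on a factual statement, that each comparison has its own specified alternative, and eight hypotheses do not obviously supply alternatives for 33 measures. Even if they did, fixing a test in advance prevents selective choice of tests; it does not limit the number of false positives when many are run.

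These tests decide whether the intervention changed what women ate. The Discussion makes that important: a null microbiota result can be read only if one knows whether participants learned and changed behaviour. No diet measure is named as decisive, so any of the 33 could be cited as evidence of dietary change. A chance finding would also set off a mediation analysis.

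**Working it through.** **1. Reproduce the counts** (from Dietary Intake).
- DGI-13: 1 total + 13 subscores = 14.
- Macronutrients: energy, protein, carbohydrate, fat, saturated fat, fiber = 6.
- SDQ: 1 total + 1 variety + 9 subscores + 2 (prebiotic, probiotic) = 13.
- Sum: 14 + 6 + 13 = 33.

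All three counts agree with the analysis section. The two-period time trends for short-term diet quality and for prebiotic and probiotic foods may add comparisons; they are not counted here.

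**2. Map measures to hypotheses**, giving the umbrella hypothesis (1) its widest reading.

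| Hypothesis | Measures | Number |
|---|---|---|
| (1) guideline accordance | 14 DGI-13, SDQ total, 9 SDQ subscores | 24 |
| (2) variety | SDQ variety score | 1 |
| (3) fiber, (7) saturated fat, (8) energy | one nutrient each | 3 |
| (4) prebiotic, (5) probiotic | one SDQ score each | 2 |
| none | protein, carbohydrate, total fat | 3 |

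Covered: 24 + 1 + 3 + 2 = 30. Not covered: 33 − 30 = 3. Of the 24 under (1), 13 + 9 = 22 are subscores with no alternative of their own, though a few may bear on (2), (6) or (7). Hypothesis (6), refined processed foods, has no measure named for it.

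**3. Error across the set if no measure is affected**, each test at its nominal level.
- Expected positives, whatever the correlation: 33 × 0.05 = 1.65.
- In the hypothesised direction only: 33 × 0.025 = 0.825, about 0.83.
- At least one two-sided positive, independent tests: 1 − 0.95^33 = 0.816.
- At least one in the hypothesised direction, independent tests: 1 − 0.975^33 = 0.566.

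For equally correlated normal statistics with correlation ρ, the two-sided chance is 1 − E{[Φ((z − √ρ·U)/√(1−ρ)) − Φ((−z − √ρ·U)/√(1−ρ))]^k}, with U standard normal and z = 1.96. The article gives no correlations, so these values of ρ are assumptions.

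| ρ (assumed) | k = 33 | k = 8 |
|---|---|---|
| 0 | 82% | 34% |
| 0.3 | 69% | 30% |
| 0.5 | 53% | 25% |
| 0.7 | 35% | 19% |

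The column for eight shows the position if each hypothesis were tested once, still unadjusted; the expected number of false positives is then 8 × 0.05 = 0.4.

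**The case against.** The strongest reply is that hypothesis (1) is broad and the subscores are defined guideline by guideline, so 30 of the 33 measures can be placed under some directional alternative. That stands. A reader might infer from eight against 33 that the rationale is untrue for most of the measures; the article does not support that. It is false for three. For the 22 subscores the weaker statement holds: a shared umbrella does not give each its own alternative.

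Second, these are secondary outcomes in a trial of 90 women, and the lack of adjustment is openly declared. The primary claim is a single test of the infant Shannon index, and its type I error is untouched. The Discussion rests its expectation of dietary change on fiber, prebiotic and probiotic foods, each with its own hypothesis. All of this stands and limits the weight of the point. But the article does not label the diet tests exploratory: it declares significance at P<.05 and defends that with a reason that does not deliver error control.

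Third, 82% needs independence, whereas totals contain subscores and the two instruments overlap. That stands too; 82% is an upper reference, not this trial's error rate.

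A reader might also see an inconsistency with the Gut Microbiota section: "Differential abundance testing with a false discovery rate correction will be performed to explore OTUs that are different between groups". There is none. That is a screen without taxon-level hypotheses, whereas the waiver is for outcomes said to be hypothesised. Finally, open-label self-report is a separate bias that no multiplicity correction would remove.

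**Conclusion.** The point holds in limited form. The reason given for no correction is wrong for protein, carbohydrate and total fat, supplies no individual alternative for the 22 guideline subscores, and would not control error across the set even if every measure had its own hypothesis. With no effect on any measure, 1.65 nominal positives are expected, 0.83 of them favouring the intervention, and at least one two-sided positive has a chance of roughly 35% to 69%. That range rests on a global null and on assumed equal correlations of 0.7 to 0.3.

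What is at stake is the claim of dietary change and the mediation analyses that follow from it. The primary comparison is not affected. Nor does the article support ranking the DGI-13 total as the sole key diet outcome. The DQES, from which it is scored, is collected only at baseline and 4 weeks after birth, while the hypotheses also speak of change sustained through pregnancy, which only the repeated SDQ can follow.

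**What to change.** Map each of the eight diet hypotheses to one named measure. Where both DGI-13 and SDQ apply, the sponsor should choose and give the reason; hypothesis (6) needs a measure named for it. Limit significance claims, and the trigger for the mediation analyses, to those eight.

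Report protein, carbohydrate, total fat and the individual subscores not so named as exploratory estimates with confidence intervals, or under the false discovery rate control already planned for OTUs. Delete the sentence justifying no correction, or restrict it to the eight mapped measures. If those eight stay unadjusted, state that they are not controlled for multiplicity.

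This changes wording only; no data collection is involved. Follow-up ended in October 2017 and the article says results are not yet written, so the mapping should be dated and its timing relative to any look at the diet data by group stated. The cost is that some nominal findings lose the significant label.
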